#### Data analysis

For data collection purposes, *trade product pack terms* are used, allowing data collection personnel to search and select on branded or generic names of products, for example:Panadeine Caplet® (codeine phosphate hemihydrate 8 mg + paracetamol 500 mg) tablet: film-coated, 12 tablets.

Use of the AMT allows linkage between trade product pack terms with other formal definitions such as the *medicinal product pack term*:paracetamol 500 mg + codeine phosphate hemihydrate 8 mg tablet, 12 tablets; and *the medicinal product term*:paracetamol + codeine.

Following data collection the trade product pack terms will be matched with both the medicinal product pack and medicinal product terms (using the SNOMED CT-AU v1.7 Common Release). AMT is also compatible with PBS data and hence the PBS dataset will be merged, along with the Anatomical Therapeutic Chemical (ATC) classification system number, into the bin audit database. This allows PBS items to be matched with a price (Manufacturer’s ‘Ex-Manufacturer Price’ for a manufacturer’s pack).

Automated matching will not be possible for manually entered items (where no trade product pack listing was available at data entry), requiring manual matching in some instances. Following data matching, audit data will be cleaned in preparation for visualisation and descriptive data analyses. Using a number of assumptions an extrapolated value of ‘wastage’ to the PBS will be estimated. This estimate is sensitive to the definition of waste, such as whether only unopened packs are counted, whether products were expired at the time of counting (but not necessarily at the time of disposal), and if a dispensing label was visible. Four assumptions will be tested and presented alongside the main results: i) dispensed, unopened, not expired; ii) dispensed, unopened, expired and not expired; iii) dispensed, opened and unopened, and not expired; and iv) dispensed, opened and unopened, expired and not expired.

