#### Data collection and training

Data collection tools and protocols developed specifically for the 2013 NatRUM audit were reviewed and refined to ensure that the audit will build on, and extend, the evidence base; e.g. whether medicines have been used (opened or full pack) and calculating the proportion of medicine that is returned (compared with 2013 where all medicine packs were treated as unopened and 100% contents were assumed) [20]. Additional variables were identified from a similar audit in New Zealand (DUMP project [22]) and in consultation with the NatRUM Ltd. Board. Table 2 outlines the variables, to be included in the audit. A purpose-built database has been developed in Microsoft Access®. We used Australian Medicines Terminology (AMT) - a subset of the SNOMED CT-AU clinical terminology, supported by the Australian Digital Health Agency (http://www.digitalhealth.gov.au/get-started-with-digital-health/what-is-digital-health/clinical-terminology remove extra line here and rejoin sentence). This national terminology unambiguously identifies branded and generic medicines commonly used in Australia. It includes a list of most prescription and OTC medicines and complementary products sold in Australian pharmacies, allowing generic and/or trade names to be easily searched and data such as form, strength and original quantity to be easily selected. For items not available in this list, manual entry of the name of the product, form, strength and original pack quantity will be required. The database and data collection process have been piloted with three RUM bins at the Queensland incineration plant and a number of modifications were implemented. The Access® database has been loaded onto laptop computers for data entry in real time at each incineration site.

**Table 2 Tab2:** Variables to be included in RUM audit and post-audit analyses

Characteristics of RUM bins	Source of container (state or territory)
	Container weight
	Percentage filled
Content of RUM bins	Medicine characteristics
	Brand name
	Generic name
	Manufacturer
	Medicine schedule (i.e. unscheduled, S2, S3, S4 or S8)
	Therapeutic category (PBS code)
	Medicine dose
	Form of medicine
	Whether medicine is PBS subsidised or private
	Whether medicine is expired
	Packaging of medicine included
	Evidence of attempted destruction for S8 medicines
	Presence of inappropriate items (e.g. sharps, rubbish)
	Complementary and alternative medicines
	Medicine in a sample package

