	Medicines characteristics once dispensed
	Year dispensed^a^
	Quantity dispensed^a^
	Quantity returned^a^
	Evidence of medicine use^a^
	Proportion of dispensed quantity unused^a, b^
	Medicine unlabelled
	Category of medicine dispensing (e.g. concession or general)^a^
	Dose administration aids (DAA)
	Type of DAA
	Proportion of medicines unused in DAA

*PBS = Pharmaceutical Benefits Scheme; S2 = Pharmacy medicine; S3 = Pharmacist-only-medicine; S4 = Prescription medicine; S8 = Controlled medicine*

^a^
*These variables extend the evidence base of data collected during the 2013 audit*

^b^
*Only medicines packaged as foil strips/blisters will be counted and assumptions used in the New Zealand DUMP project audit* [22] *will be applied to documentation of quantity of returned inhalers, creams, liquids*

Audit training tools, including a data collection protocol and quality assurance procedure, and Occupational Health and Safety (OH&S) Standard Operating Procedure (SOP) were developed in consultation with incineration plant managers, personnel from Griffith University OH&S and NatRUM Ltd. (all training tools and protocols are available from correspondence author on request).

Data collection will be conducted at each of the three incineration sites by research assistants, working in pairs (one person inspects and counts whilst the second enters the information into the database), under the supervision of the project Data Collector Manager, (a registered pharmacist). An additional research assistant will be available at each site to act in a quality control role and to provide cover for breaks and/or absences such as unexpected illness. Data collectors will be trained at each site to safely audit a RUM bin and to enter data into the Access® database. Training will include familiarisation with the specific auditing equipment including protective clothing (gloves, safety glasses, dust masks, coveralls), and tools (tongs, tweezers, scales), and a demonstration of how to safely open and assess the contents of a RUM bin. Training will also emphasise the importance of the confidential nature of bin contents including any pharmacy, prescriber and patient information. A representative from Griffith University OH&S will be present for this training.

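### The value of wastage to the PBS rests on a manufacturer's pack price, and none of the four planned scenarios shows how that differs from what the PBS paid

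*Protocol article*

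**What the plan says.** The Study design overview gives Stage One two linked aims: to find what share of the waste is PBS-subsidised, and to extrapolate the value of that waste to the PBS.

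The Stage One Data analysis section explains how items acquire a value. Audit terms are linked to PBS data by product: "AMT is also compatible with PBS data and hence the PBS dataset will be merged". The price follows from that link: "This allows PBS items to be matched with a price". The price named there is the ex-manufacturer price of a manufacturer's pack. No other price, patient contribution, mark-up or fee is mentioned.

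The section then says: "Using a number of assumptions an extrapolated value of ‘wastage’ to the PBS will be estimated". On uncertainty it says: "This estimate is sensitive to the definition of waste, such as whether only unopened packs are counted". The other sensitivities it names are expiry at the time of counting and whether a dispensing label was visible. Four scenarios will be presented. All require the item to have been dispensed, and they differ only in whether opened packs and expired packs are included.

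Table 2 (Data collection and training), whose title covers both the audit and the later analyses, lists "Whether medicine is PBS subsidised or private" and, among the characteristics once dispensed, "Category of medicine dispensing (e.g. concession or general". The section on bin and contents inspection also has the auditors record whether a dispensing label is present, the dispensing category and the year dispensed.

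**The concern.** Value to a subsidy payer and the manufacturer's price of a pack are different quantities. Matching a product to the PBS dataset shows that it is listed and what the manufacturer's pack costs. It does not show who paid for that supply or how much the scheme contributed.

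The scenarios will probably be read as the uncertainty around the dollar figure. They all use the same price basis, so their spread describes only the rule for what counts as waste. The distance between product price and PBS outlay is invisible in all four.

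The Abstract says the results will inform the Federal Department of Health and the scheme's Board. Readers there would naturally take a value to the PBS as money the scheme spent on medicines that came back unused. The study collects two fields that bear directly on this, but the described valuation uses neither.

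**Working it through.** **No figure to reproduce.** The article states no wastage value, unit price, patient contribution, fee or private share. The check is therefore a comparison of the text, followed by a sensitivity identity with assumed inputs.

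**Text side by side.**
- Target (Study design overview): value to the PBS, a payer quantity.
- Measure (Stage One, Data analysis): ex-manufacturer price of a pack, a product quantity.
- What the scenarios vary: opened or not, expired or not. Price, payer and dispensing category appear in none of them.
- What is collected (Table 2; bin and contents inspection): PBS/private flag, dispensing category, year dispensed.

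**Identity.** For each 1.00 of ex-manufacturer value,

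PBS outlay / ex-manufacturer value = (1 − q) × max(0, 1 + f − c)

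where
- q = share of the priced value that was supplied privately;
- f = mark-ups and fees divided by the ex-manufacturer price;
- c = patient contribution divided by the ex-manufacturer price.

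All three are assumptions. So is the structure, in which the scheme pays price plus fees less the patient's contribution and never less than zero. The article does not describe how PBS payment works.

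**Results.**

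| q | f | c | Calculation | Ratio |
|---|---|---|---|---|
| 0 | 0 | 0 | 1 × 1.00 | 1.00 |
| 0 | 0 | 0.25 | 1 × 0.75 | 0.75 |
| 0 | 0 | 0.5 | 1 × 0.50 | 0.50 |
| 0 | 0 | 1 or more | floored at zero | 0 |
| 0 | 0.5 | 0 | 1 × 1.50 | 1.50 |
| 0 | 0.5 | 0.25 | 1 × 1.25 | 1.25 |
| 0 | 0.5 | 1 | 1 × 0.50 | 0.50 |
| 0.10 | 0 | 0.25 | 0.90 × 0.75 | 0.675 |
| 0.20 | 0 | 0.5 | 0.80 × 0.50 | 0.40 |
| 0.20 | 0.5 | 0.25 | 0.80 × 1.25 | 1.00 |

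**Reading.** With q = 0 the two quantities agree only when f = c. Otherwise they agree only when the terms happen to cancel, as in the last row. With no fees, the ex-manufacturer figure is at or above the outlay. With q = 0 and fees larger than the contribution, it falls below the outlay. Scaling the sample to the national level multiplies both quantities by the same factor and leaves the ratio unchanged. None of the four scenarios changes f, c or q, so none reveals the ratio.

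**The case against.** The strongest defence is that the article openly names its price basis, puts the word wastage in quotation marks and says the estimate rests on assumptions. Valuing medicines at one disclosed product price is a legitimate costing choice, and a condensed article may leave the costing algorithm to a fuller document. Part of this stands: a payer filter or a contribution offset could be among the unlisted assumptions. It does not remove the point, because the price and the four tested scenarios are stated choices, and together they do not measure or probe a value to the PBS.

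Three stronger readings are tempting, and the article does not support them.

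- *Private supplies are counted as PBS waste.* A reader might infer this because the scenarios require only that an item was dispensed. The article never says so. The objective refers to PBS-subsidised waste, Table 2 lists the PBS/private flag for use in the analyses, and the scenarios are introduced as definitions of waste rather than of payer. What can be said is that no scenario states that private items are excluded.
- *The pack price will be multiplied by the fraction of the dispensed quantity left over.* Table 2 does list "Proportion of dispensed quantity unused". However, no section describes that multiplication. Quantity dispensed and quantity returned are separate variables, pack size is recorded and unit doses are counted exactly, so correct per-unit pricing is possible.
- *The figure overstates the cost to the PBS.* Contributions and private supply push that way, but mark-ups and fees push the other way. The article gives none of these amounts.

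It is also only partly true that the collected fields are enough to correct the figure. The flag, category and year are collected. Contribution amounts, mark-ups and fees are not among the listed variables, and category and year probably depend on a readable label.

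**Conclusion.** The point holds in a limited form. The objective is a payer's value, the only price named is a product price, and the planned scenarios cannot show the difference between them. The fields for payer and dispensing category are collected but are given no place in the described valuation.

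The direction and size of the difference cannot be settled from the article. The range of 0 to 1.5 times the ex-manufacturer value follows from the assumed inputs above (f from 0 to 0.5, c from 0 upwards) and from the assumed payment structure. It illustrates how far apart the two quantities can lie and does not estimate the error in this study.

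The fault lies in the labelling and in the sensitivity set. Bin sampling and the counts of returned medicines are unaffected.

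**What to change.** 1. Label the present figure *ex-manufacturer value of returned PBS-listed medicines*, and keep the four scenarios as sensitivity to the definition of waste.
2. State that the PBS figure is restricted to items flagged as PBS-subsidised, and report private items separately. Say whether the flag records how that supply was paid for or only that the product is listed, since Table 2 places it with the product's characteristics and not with those recorded once dispensed.
3. Add one sensitivity result for net cost to the PBS: price plus applicable mark-ups and fees, less the patient contribution for the recorded dispensing category and year. Apply the floor at zero to each supply before summing. Where category or year cannot be read, give a low and a high value in place of a single imputed one.

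Relabelling costs a sentence. The net-cost result needs contribution and fee schedules from outside the audit, linkage by category and year, and a bounded assumption for unreadable labels. The reported value may move in either direction. Sampling and data collection need no change, provided the flag is recorded for each supply.

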### Stage two

#### Step one

The first step of Stage Two is a 10-min online general population survey conducted with a representative sample of the Australian population, aged over 18 years.

##### Participants

An experienced research panel company (Research Now®) have been contracted to undertake the data collection with an existing panel of individuals who represent the Australian adult population. Research Now® will invite participation to achieve a national representative sample based on gender, age and geographical location from the most recent census (2011) data (Table 3) [25].

**Table 3 Tab3:** General population survey sample characteristics

	Australian representative sample [25] %	Survey sample targets for *N* = 4302 n
Gender		
Female	51	2193
Male	49	2107
Age range (years)		
18–24	12	516
25–34	18	774
35–44	19	817
45–54	18	774
55–64	15	645
65–99	18	774
State or territory		
Australian Capital Territory	2	86
New South Wales	32	1376
Northern Territory	1	43
Queensland	20	860
South Australia	7	301
Tasmania	2	86
Victoria	25	1075
Western Australia	10	430

The most recent Australian Bureau of Statistics survey about waste disposal practices (conducted in March 2012) included data from 12,870 households. This survey used a multi-stage area sampling method [21]. A sample size of 4300 is proposed for our general population survey to enable comparison with the Australian Bureau of Statistics survey results.

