In July 1998 the Australian Government also introduced a program that provides a safe, free, and convenient means for the public to return unwanted and out-of-date medicines to community pharmacies; the National Return and Disposal of Unwanted Medicines (NatRUM) scheme. The medicines collected in specific RUM (Return of Unwanted Medicines) bins are then disposed of by high-temperature incineration (which is the Environment Protection Authority (EPA) approved method of disposal) [18]. However, whilst national medicine collection and disposal schemes that are free for the public, such as the Swedish and Australian programs, are becoming more common (e.g. in the United Kingdom and European Union), these are not standard in all countries.

Incineration of medicine waste collected via the Australian NatRUM scheme has increased considerably over time; in the 2015/2016 financial year 705,079 kg of medicine waste was incinerated, an increase of 7.7% compared with the previous year [18]. Two reviews of the NatRUM scheme were undertaken in 2005 and 2013 [19, 20]. The 2005 study interviewed a sample of 605 consumers returning unwanted medicines to community pharmacies in one state of Australia. Most of these consumers had used the NatRUM scheme previously after being informed about it by a pharmacist. The main reasons for consumers to return medicines were: because it had expired (31%), person taking medicine (usually a relative) was deceased (26%), or the medicine (prescription) had been changed (8.5%) [19]. The 2013 study was a medicine wastage audit of a random sample of 686 RUM bins collected from six regions of Australia. Most of the returned medicines were scheduled (e.g. prescription, pharmacist-only, or pharmacy-only medicines), and almost half were still within their expiry date [20]. Six of the 10 most commonly returned medicines were also the most frequently dispensed under the Pharmaceutical Benefits Scheme (PBS).^1^

Despite this increasingly used nation-wide scheme, information about household waste disposal practices from the Australia Bureau of Statistics in 2012 estimated that more than one million Australian households had discarded unwanted medicines, drugs or ointments with their usual garbage [21]. For households who had disposed of these items in the last 12 months, 55% had disposed of them with the usual household garbage and 14% had poured them down the drain or toilet [21].

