##### Survey and data collection

The survey questions were developed using Australian Bureau of Statistics tools (the 2012 Waste Management questions and the 2014–2015 National Health survey [21, 26]), relevant literature [19, 22], and input from the NatRUM Ltd. Board (available on request from correspondence author).

The survey is designed to take around 10 min to complete. The questions have multiple-choice options with a free-text response available when the ‘other’ option is selected. It consists of:11 demographic questions (e.g. age, gender, state/territory, country of birth, language spoken at home, living arrangements, education, employment, household income);Four questions on whether respondents currently have unwanted (used, unused or expired) medicines in their home, the type of medicines retained (prescription, OTC, complementary and/or alternative) and why they have retained them;Three questions on disposal practices (whether respondents have disposed of any in the last 12 months, how they disposed of them and why). The questions on disposal practices have been included from the Australian Bureau of Statistics with minimal changes to allow for comparison of results [21];Two questions on awareness and use of the NatRUM scheme. Respondents who are not aware of the NatRUM scheme are provided with a brief overview of the scheme, and a link to the website (www.returnmed.com.au), and asked if they would use the national scheme in the future:Respondents are also asked to indicate whether they are healthcare workers, with a further four questions relating to the advice they give to their patients about medicines disposal.

Finally, two ‘ranking’ questions will assess a potential social marketing strategy designed to inform better use of the NatRUM program. The first question relates to concerns about storing and disposing of unwanted medicines, the second addresses the best media for the promotion of associated public health messages. In the online version of the survey the order of response options for these two questions will be randomised. Survey respondents will be asked to rank the statements in order of most important/effective to least important/effective.

The survey has been piloted (in hardcopy) with two members of the NatRUM Ltd. Board and seven people from the general population with medicines in their homes who were known to the research team. Minor amendments to the wording and question order were subsequently made.

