Working with Research Now®, a user-friendly survey which could be completed on-line, or using mobile devices such as smartphones, was developed. For all questions with six or more multiple-choice options the option list is randomised. The online survey has been soft-launched with 48 panel members to test the response algorithms. For the survey proper, Research Now® will invite participation from its panel members to ensure good sample representation and adjust when necessary to ensure targets for under-represented groups (e.g. younger people) are met for the survey sample (*n* = 4300). Survey respondents will be provided with compensation for their time in accordance with terms of their enagagement with Research Now®.

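### The survey size is justified by comparison with a household survey, but adults are sampled to person-level quotas, so homes with more adults are over-represented and the reporting unit is unclear

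*Protocol article*

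**What the plan says.** Under Stage two, Step one, Participants, the sample size has a single stated basis: "A sample size of 4300 is proposed for our general population survey to enable comparison with the Australian Bureau of Statistics survey results". The same paragraph says that the benchmark "included data from 12,870 households" and adds: "This survey used a multi-stage area sampling method". The Background gives its results per household: "For households who had disposed of these items in the last 12 months, 55% had disposed of them with the usual household garbage", with a further 14% using the drain or toilet.

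The new survey draws on a commercial panel of individual adults, with targets for gender, age group and state taken from census shares of people (Table 3).

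The article describes the unit of the answers in three ways:
- The Study design overview labels Step One a household survey and sets household disposal as an objective.
- Survey and data collection describes an item on "whether respondents have disposed of any in the last 12 months".
- The same section says that the disposal items were taken from the benchmark almost unaltered so that results can be compared.

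The Data analysis section for Step one calls most analyses descriptive and does not mention weights. Table 3 is headed "Survey sample targets for *N* = 4302 n", whereas the text uses 4,300.

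**The concern.** A sample of households gives each home one entry. A sample of adults gives a three-adult home about three times the chance of entry of a one-adult home. If disposal habits differ by household size, the two designs estimate different percentages even when the question is worded identically. A difference from 2012 could then partly reflect the sampling unit. The near-copied wording does not remove this, because the effect comes from how respondents are selected.

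Two further points bear on how the comparison is read. If the unit of the answer is not fixed, the comparison has no single meaning. And the 55% and 14% are shares among those who disposed, so the n behind the comparison is smaller than the survey n on which it is said to rest.

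**Working it through.** **The stated figure.** N = 4,300 comes with no margin of error, power or difference to detect, so it cannot be reproduced. A fuller document may hold that basis, so its absence is not counted as an error here.

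**Selection by household size.** Assume that 33%, 52% and 15% of homes have 1, 2 and 3 adults. The article gives no such figures.
- Mean adults per home = 0.33×1 + 0.52×2 + 0.15×3 = 1.82.
- Shares in a sample of adults: 0.33/1.82 = 18%, 1.04/1.82 = 57%, 0.45/1.82 = 25%. One-adult homes fall from 33% to 18%.

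**Effect on the garbage share.** Assume that every respondent answers for the household, with a share of 55% in two-adult homes and a constant change per additional adult.

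| Change per adult | Household-based share | Adult-sampled share | Shift |
|---|---|---|---|
| 0 points | 55.0% | 55.0% | 0 |
| 5 points (50, 55, 60%) | 54.1% | 55.3% | 1.2 points |
| 10 points (45, 55, 65%) | 53.2% | 55.7% | 2.5 points |

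Example, second row: household-based 0.33×50 + 0.52×55 + 0.15×60 = 54.1. Adult-sampled (0.33×50 + 1.04×55 + 0.45×60)/1.82 = 55.3. The shift reverses sign if the share falls with household size.

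**Cost of weighting by 1/adults.** Design effect = (mean of 1/adults over homes) × (mean adults per home) = (0.33 + 0.52/2 + 0.15/3) × 1.82 = 0.64 × 1.82 = 1.16. Effective n = 4,300/1.1648, about 3,690.

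**Number behind the 55%.** The proportion who will have disposed is not given; assume 20–40%.
- n = 0.20×4,300 = 860 to 0.40×4,300 = 1,720.
- 95% margin at 55% = 1.96×√(0.55×0.45/n): 3.3 points at 860 and 2.4 points at 1,720. All 4,300 would give 1.5 points.
- With the design effect, multiply by √1.1648 = 1.08: about 3.6 and 2.5 points.

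**Scale.** For 4,300 against 12,870 under simple random sampling, two-sided 5% and 80% power (all assumed), the detectable difference from 55% is about 2.5 points. If only 20–50% of both samples disposed, it is about 5.5 to 3.5 points. The largest illustrated shift therefore matches the full-sample figure and is below the figure for disposers.

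**Table 3.**
- Gender: 2193 + 2107 = 4,300.
- Age: 516 + 774 + 817 + 774 + 645 + 774 = 4,300.
- State: 86 + 1376 + 43 + 860 + 301 + 86 + 1075 + 430 = 4,257. The state percentages sum to 99, and 0.99×4,300 = 4,257.
- Every cell is its rounded percentage × 4,300, so 4302 is the base of no block. For example, 51% of 4302 is 2194, against 2193 printed.
- The shortfall is 43/4,300 = 1.0%. The 95% margin at 50% moves from 1.49 to 1.50 points.

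**The case against.** The best defence is that the article already aims at the household. It calls Step One a household survey, states a household objective and reuses the benchmark items almost unchanged. A person answering for a home is still a respondent, and the questionnaire is not shown. Weights are commonly left to an analysis plan, and living arrangements are collected, so an adjustment may be possible already.

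Much of this stands, and it rules out several stronger readings:
- **That the items are person-level.** A reader might infer this from the word respondents, and might add that if two adults each dispose independently with probability 15%, the household figure is 1 − 0.85² = 28%. The article is inconsistent on the unit rather than clearly person-level. The 15% and the independence are assumptions. The contrast also concerns whether anything was disposed of, whereas 55% and 14% are shares of method among disposers.
- **That the analysis will be unweighted.** The article is silent on weights, which is not a decision against them.
- **That the plan claims a margin of 1.5 points.** It states no margin for the survey.
- **That the quotas cannot be met.** Table 3 gives targets, and the panel company may adjust recruitment. All state targets can be filled, leaving 43 of 4,300 places without one.

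The selection effect survives the defence. It follows from recruiting adults to person-level quotas, whatever the questions say. The Limitations section acknowledges panel selection bias but not the difference in unit.

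**Conclusion.** The concern holds in a limited form. The only stated reason for 4,300 is comparison with a household survey, yet the sample is one of adults, so homes with more adults are over-represented in that comparison. The reporting unit also needs to be made consistent across the article.

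The illustrated shift is 0 to 2.5 points. It rests on assumed household sizes and assumed variation of the garbage share with household size, and it is zero if habits do not vary with size. That is modest, but large enough to blur a small change since 2012. The n for the method comparison is below 4,300 for certain; 860 to 1,720 is the range only if 20–40% disposed.

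The Table 3 discrepancies are real but are a 1% rounding shortfall and a heading that differs by 2, with negligible effect on precision. The documents do not support saying that the survey measures the wrong thing, that weighting has been ruled out or that recruitment will fail.

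**What to change.** 1. Reconcile the Study design overview, Participants, and Survey and data collection sections so that the disposal items used for the comparison are reported for the household, and confirm that the wording matches the benchmark items on this.
2. For that comparison only, weight each respondent by 1/number of adults in the home and show the result beside the unweighted one. Take the count from the living-arrangements question if it gives it; otherwise add one item before the survey proper.
3. State that the 55% and 14% comparisons use only those who disposed, and give the expected n and precision on that base.
4. Use one N throughout, and recompute the state targets from unrounded census shares so that all three blocks sum to it.

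The cost is at most one questionnaire item, one weighted table and a corrected Table 3. The downside is a modest loss of precision in the weighted comparison: under the assumed household sizes, margins widen by about 8%.
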